#### Strategies to improve adherence to interventions

Adherence will be assessed by having the patients maintain a daily log of medication during the observation period.

#### Relevant concomitant care permitted or prohibited during the trial

During the study period, changes in medications other than the addition of BBG9-1 to the intervention group will not be permitted except in unavoidable circumstances.

#### Provisions for post-trial care

Post-trial care is not planned. The possible risks are detailed in the informed consent form. If any patient harmed during the trial, appropriate medical and nursing care will be provided.

#### Outcomes

The primary endpoint of this trial will be the change in the total GSRS score from baseline to follow-up examination (12 ± 3 weeks after baseline examination). Secondary endpoints of this trial will be as follows: (1) change and percent change in following parameters from baseline to follow-up examination: GSRS subdomain scores, fecal properties/Bristol stool form scale, defecation frequency, blood test biomarkers (total bile acid, glycoalbumin, glucagon-like peptide-1, glucose-dependent insulinotropic polypeptide, glucagon, HbA1c, fasting plasma glucose, C-peptide, AST, ALT, gamma-glutamyltransferase, total cholesterol, high-density lipoprotein cholesterol, low-density lipoprotein cholesterol, triglycerides, blood urea nitrogen, and creatinine), physical examination (body weight and body mass index), urinary albumin creatinine ratio, gut microbiota (type of enterobacteria, relative abundance, alpha diversity, and beta diversity), macronutrients (total energy, carbohydrate, fat, protein, and dietary fiber intakes measured by brief-type self-administered diet history questionnaire [BDHQ]) [16]; (2) proportion of participants whose fecal property of Bristol stool form scale is within normal range (3.5–4.5); (3) medication adherence to the BBG9-1; (4) factors that affect GSRS total score or constipation/diarrhea subdomain scores; (5) stratification of following items by baseline symptoms (constipation/diarrhea): GSRS total score, GSRS subdomain scores, proportion of participants whose fecal properties are within normal range, defecation frequency, blood test biomarkers, and gut microbiota. The exploratory endpoints of this trial will be as follows: (1) blood, urine, and stool metabolomes (short, medium, and long chain fatty acids, amino acids, carbohydrates, and bile acids); (2) items other than nutrients evaluated in the secondary endpoints and items evaluated by the diabetes treatment satisfaction questionnaire (DTSQ) [17]; (3) items other than physical examination evaluated in the secondary endpoints; (4) items other than gut microbiota evaluated in the secondary endpoints; (5) change in lipopolysaccharide-binding protein; (6) subgroup analysis by age, sex, etc. Harm outcomes will also be evaluated based on various laboratory abnormalities and adverse reactions to the medication.

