### Statistical methods

#### Statistical methods for primary and secondary outcomes

Full analysis set (FAS) analysis will be performed for the primary and secondary endpoints. If necessary, per protocol set (PPS) analysis will be performed as a sensitivity analysis for the FAS analysis. In principle, the analysis should be performed at a two-sided significance level of 5%. The person responsible for the statistical analysis will prepare a separate statistical analysis plan that specifies the details of the statistical methods, including data handling. A statistical analysis plan will be prepared before the data are fixed. The primary endpoints will be treated as validation results, whereas the other endpoints will be treated as exploratory results.

The FAS will include the participants who are enrolled in the study and assigned to the study treatment. However, data on participants who violated the research protocol, such as enrolment without consent and registration outside the contract period, will be excluded. The PPS will include research participants who will be excluded from the FAS for the following reasons: violation of eligibility criteria, violation of exclusion criteria, violation of concomitant use of prohibited medications, and medication compliance rate > 120% or < 75%. The safety analysis set will include participants in whom research treatment has been initiated.

Summary statistics for the background data of study participants will be calculated for each group. Comparisons between groups will be made using the χ-square test or Fisher’s direct probability test for categorical variables and the two-sample t-test or Wilcoxon rank-sum test for continuous variables.

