The primary endpoints will be evaluated using analysis of covariance. A two-sample t-test will be performed for between-group comparisons and a one-sample t-test will be performed for within-group comparisons. The secondary endpoints will be evaluated using a two-sample t-test or one-sample t-test. For data without a normal distribution, the log-transformation will be attempted; however, if it does not improve the distribution, Wilcoxon rank-sum test or Wilcoxon signed-rank will be performed. For the Bristol scale score, between-group comparisons will be performed using the Wilcoxon rank-sum test, and within-group comparisons will be performed using the Wilcoxon signed-rank test. For percentage endpoints, the χ-square test or Fisher’s direct probability test will be performed. For safety, a list of all adverse events will be prepared for each group in the safety analysis population; if necessary, comparisons between groups will be made using Fisher’s direct probability test.

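### Within-group one-sample tests of mean percent change give too many false increases for the more variable ratio-scale secondary parameters

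*Protocol article*

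**What the plan says.** In the Outcomes section, item (1) of the secondary endpoints reads "1) change and percent change in following parameters from baseline to follow-up examination: GSRS subdomain scores". The list continues with the Bristol scale, defecation frequency, blood markers, body weight and BMI, the urinary albumin creatinine ratio, gut microbiota and macronutrient intakes. Items (2) to (4) are not percent changes.

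Under Statistical methods for primary and secondary outcomes, the general rule is: "The secondary endpoints will be evaluated using a two-sample t-test or one-sample t-test". The role of the one-sample test is explained in the sentence on the primary endpoint, where "a one-sample t-test will be performed for within-group comparisons".

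Non-normal data follow a sequence. First, "For data without a normal distribution, the log-transformation will be attempted". Then, "if it does not improve the distribution, Wilcoxon rank-sum test or Wilcoxon signed-rank will be performed". The Bristol score has its own rule: "For the Bristol scale score, between-group comparisons will be performed using the Wilcoxon rank-sum test", with a signed-rank test within groups.

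The same section sets a two-sided 5% level and treats every endpoint other than the primary as exploratory. It leaves further detail to a separate analysis plan that is not shown.

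**The concern.** Percent change is asymmetric. A patient who goes from 3 to 6 stools a week scores +100%, and one who goes from 6 to 3 scores -50%. Together they average +25% although nothing has changed overall. Ordinary within-person variation does the same across a whole group: follow-up divided by baseline has an expectation above 1 even when the two values are exchangeable. A one-sample t-test of mean percent change against zero is then aimed at a null value that is wrong when there is no effect.

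At stake is the reading of the within-arm results. In an open-label trial that also seeks evidence on mechanism, a significant rise of a gut hormone or of defecation frequency in the BBG9-1 arm is easily taken as a drug effect. Because the bias grows with a parameter's variability, the noisiest parameters would look the most responsive.

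**Working it through.** **Inputs from the protocol.** The group size is 45 evaluable patients (Sample size section). It reproduces: with difference 0.244, SD 0.412, two-sided alpha 0.05 and power 0.80, n = 2 × (1.960 + 0.842)² × 0.412² / 0.244² = 44.8, so 45 per group, and 45 / 0.9 = 50 with dropout. The protocol states no error rate or bias for percent change and no within-person variability for any secondary parameter.

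**Assumptions.** Baseline and follow-up are log-normal with the same mean, log-SD s from 0.1 to 0.8 and correlation r = 0.7. There is no true change.

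**Bias.** The log ratio of follow-up to baseline is normal with mean 0 and variance 2s²(1 − r). Hence the expected mean percent change is exp(s²(1 − r)) − 1. For s = 0.5 this is exp(0.25 × 0.3) − 1 = exp(0.075) − 1 = +7.8%.

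**Error rate of within-group tests** (simulation, n = 45, two-sided 5%):

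| s | Expected mean percent change | One-sample t on percent change | One-sample t on log ratio |
|---|---|---|---|
| 0.1 | +0.3% | about 6% | about 5% |
| 0.3 | +2.7% | about 9% | about 5% |
| 0.5 | +7.8% | about 18% | about 5% |
| 0.8 | +21% | about 36% | about 5% |

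At the three larger values of s, nearly all the errors are false increases. With r = 0.8, the t-test error at s = 0.3, 0.5 and 0.8 is 8%, 13% and 27%.

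**The planned sequence for non-normal data.** About half of the percent changes are negative when nothing changes, so percent change cannot itself be logged. If the analyst therefore goes from a failed normality check straight to the signed-rank test, the error is about 8% to 14% for s from 0.3 to 0.8. The signed-rank test assumes symmetry, which percent change lacks. If the ratio of follow-up to baseline is logged instead, the error is roughly 6% to 9%. Some inflation remains in both cases because samples that pass the normality check still go to the biased t-test. Including s = 0.1, the range is about 6% to 14%.

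**Check with another parameterisation.** With exchangeable values and a within-person CV of 5%, 20%, 30% and 50%, the t-test error is 6%, 11%, 20% and 39%. With a switch to signed-rank when normality is rejected, it is 8%, 11% and 14% at the last three.

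**Between-group test.** Both arms carry the same bias. The two-sample t-test on percent change held 4.2% to 5.4% in all settings.

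**Between-group power** (45 per arm; true ratios 0.87, 0.80 and 0.75 at s = 0.3, 0.5 and 0.8):

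| s | Percent-change t | Log-ratio t | Log-scale ANCOVA |
|---|---|---|---|
| 0.3 | 0.79 | 0.81 | 0.86 |
| 0.5 | 0.74 | 0.77 | 0.83 |
| 0.8 | 0.52 | 0.58 | 0.66 |

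The total gap is 0.07, 0.09 and 0.14. Of this, 0.05, 0.06 and 0.08 come from baseline adjustment and the rest from the scale.

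**The case against.** The strongest reply is that the plan does not prescribe an unconditional t-test. It tries a log-transformation first and rank tests after that, and the most skewed parameters are the most likely to enter that sequence. This stands in part: 18% and 36% describe the t-test alone, and the sequence brings the error down to about 6% to 14%. It does not restore 5%, and the protocol does not say which quantity is to be logged.

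Four wider readings are tempting but not supported:

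- A reader might infer that every secondary endpoint is affected. Items (2) to (4) are not percent changes, and at low variability the error is close to nominal.
- A reader might apply the point to the GSRS subdomains because they head the list. For the subdomain that qualifies a patient, entry at a score of 3 or more makes regression to the mean dominate, which produces false decreases. The Bristol score is tested by Wilcoxon methods only. Neither belongs to this point.
- A reader might infer that the randomised comparison is invalid. It keeps its level. Its power loss is largely the lack of baseline adjustment, and plain absolute change has lower power still in the same model (0.75, 0.63 and 0.35).
- A reader might take testing both change and percent change as an error in itself. For exploratory endpoints it is not, and which form leads can be settled in the separate analysis plan.

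The exploratory label also stands. It limits the consequence, but it does not make a biased test valid.

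**Conclusion.** The point holds in a narrow form. For the positive ratio-scale parameters of item (1) with sizeable within-person variation, the within-group one-sample t-test on percent change produces too many false increases: about 9% to 36% for log-SD 0.3 to 0.8, and about 6% at log-SD 0.1. Under the plan's sequence for non-normal data the excess is moderate, with a total error of about 6% to 14%. These figures rest on an assumed log-normal model, correlation 0.7 and 45 patients per arm, because the protocol gives no variability for these parameters.

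The primary endpoint is an absolute change and is untouched. This is a cheap improvement to consider, not a threat to the trial's main conclusion.

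**What to change.** In Outcomes, keep arithmetic percent change as a descriptive summary and drop it as a tested endpoint. In Statistical methods for primary and secondary outcomes, state that:

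- positive ratio-scale parameters are analysed as log follow-up with log baseline as covariate, and the back-transformed ratio of geometric means is reported as the percent effect;
- any within-group test of these parameters uses the log ratio;
- GSRS subdomains and the Bristol score are analysed as absolute change only.

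Parameters that can be zero, such as the relative abundance of a taxon, cannot be logged directly and need their own rule in the analysis plan.

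The cost is a change of wording in two sections and in the analysis plan, with no new data. The downside is that the reported percent effect becomes a ratio of geometric means and not an average of individual percentages, which needs a sentence of explanation for clinical readers.

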### Eligibility criteria

Patients must satisfy all of the following inclusion criteria. The inclusion criteria are as follows: (1) symptoms of diarrhea or constipation; (2) three or higher in Gastrointestinal Symptom Rating Scale (GSRS) subdomain score (diarrhea or constipation); (3) T2DM patients without diabetic polyneuropathy; (4) no new antibiotic usage within 12 weeks prior to consent; (5) no new diet interventions within 12 weeks prior to consent; (6) no changes in medications which can affect gastrointestinal symptoms and microbiome (addition or discontinuation of medications or change in use or dosage of medications) within 12 weeks prior to consent; (7) aged 20 and up and under 75 years or less at the time of consent; (8) written consent obtained from the individual. The exclusion criteria are as follows: patients with (1) mean defecation frequency < 1 or > 42 times/ week within 4 weeks before giving their consent; (2) structural diseases, including inflammatory diseases (infectious enteritis, diverticulitis, Crohn’s disease, and ulcerative colitis), and stenotic lesions, diagnosed by colonoscopy within 5 years before giving their consent; (3) having both ≥ 3 on the GSRS constipation subscale and > 4 on the Bristol stool scale; (4) having both ≥ 3 on the GSRS diarrhea subscale and < 4 on the Bristol stool scale; (5) gastrointestinal symptoms of both diarrhea and constipation; (6) past history of inflammatory bowel disease and celiac disease; (7) HbA1c level ≥ 9% at the time of consent; (8) use of alpha-glucosidase inhibitors within 4 weeks prior to consent; (9) cerebral infarction, stroke, or myocardial infarction within 12 weeks prior to consent; (10) severe hepatic dysfunction defined as alanine aminotransferase (ALT) or aspartate transaminase (AST) level 5 times equal or higher than the upper normal limit; (11) severe renal dysfunction defined as estimated glomerular filtration rate < 30 mL/min/1.73 m^2^; (12) active malignant tumor; (13) allergy history of bifidobacteria; (14) usage of any other supplements or medications that affect intestinal function; (15) usage of medications that are likely to cause abdominal symptoms (e.g., gastroprokinetic agents, drugs for dyspepsia, antiemetic agents, laxatives, and anticholinergics); (16) patients with changes in diet within 12 weeks prior to consent; (17) other conditions that the researcher or investigator thinks inappropriate for the study.

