### Assignment of interventions: Allocation

#### Sequence generation

The investigators or researchers will enter the necessary information into the web system; if eligible, based on the GSRS score and the Bristol scale score, perform the main enrolment/assignment, and confirm the results. The participants will be assigned to group A or group B using the minimization method, with age, sex, and type of symptom (constipation or diarrhea) as allocation factors.

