### Data collection and management

#### Plans for assessment and collection of outcomes

The researchers will manage the data of the participants using the central registry number assigned by the data center. In this study, data on study participants reported by the researchers will be collected at each observation point using a case report form (CRF), survey forms (GSRS, BDHQ, and DTSQ), logbooks (defecation frequency, stool characteristics (Bristol scale score), and adherence to BBG9-1). We will use the average of the 1-week Bristol scale scores as the Bristol scale score. The survey forms of 12-week after the baseline examination and logbooks during the observation periods will be sealed using a special envelope and sent to the data center in such a way that the investigators or researchers cannot confirm the contents of the responses. The investigators or researchers will ensure that the survey forms and logbooks other than those answered and recorded by the research participants themselves are complete in order to ensure that the data recorded by the research participants (CRFs) are not lost or destroyed. If any data correction is necessary, the date and reason for the correction shall be recorded. Researchers shall confirm that all data, including the corrected data, are accurate and complete and shall ensure the quality of the data. For data submitted in the CRF, the data management staff will maintain a central registry of all data from the site.

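### The test for the proportion with normal stool form ignores that some patients can enter already in range, which costs this exploratory endpoint some power

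*Protocol article*

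**What the plan says.** - **Endpoint (Outcomes, secondary endpoint 2).** The "proportion of participants whose fecal property of Bristol stool form scale is within normal range (3.5–4.5". This is a status proportion with no condition on the baseline value. The wording names no time point; I take it to be the single follow-up examination at 12 ± 3 weeks.
- **Entry (Eligibility criteria).** Inclusion needs "three or higher in Gastrointestinal Symptom Rating Scale (GSRS) subdomain score (diarrhea or constipation". No abnormal Bristol score is required. The Bristol score enters only through two exclusions: "having both ≥ 3 on the GSRS constipation subscale and > 4 on the Bristol stool scale" and "having both ≥ 3 on the GSRS diarrhea subscale and < 4 on the Bristol stool scale".
- **Score (Plans for assessment and collection of outcomes).** "We will use the average of the 1-week Bristol scale scores as the Bristol scale score", so non-integer values will occur.
- **Test (Statistical methods for primary and secondary outcomes).** "For percentage endpoints, the χ-square test or Fisher’s direct probability test will be performed". Analysis of covariance is named for the primary endpoint only.
- **Allocation (Sequence generation).** Minimization is done "with age, sex, and type of symptom (constipation or diarrhea) as allocation factors"; baseline Bristol score is not a factor.
- **Standing of the result (same statistical section).** The primary endpoint is confirmatory, "whereas the other endpoints will be treated as exploratory results".

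**The concern.** The eligibility cut-off (4) and the edges of the normal range (3.5 and 4.5) do not coincide. A constipation patient averaging 3.6, or a diarrhea patient averaging 4.3, is eligible and already normal. So is a patient of either type at exactly 4. If such a patient is still in range at follow-up, he or she counts towards the proportion without having changed.

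Baseline in-range status is likely to predict follow-up status strongly, and the trial records it, but the stated test for this endpoint does not use it. The planned breakdown by constipation or diarrhea does not help, because both groups can contain in-range patients. What is at stake is the precision and readability of one secondary result.

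**Working it through.** **1. Overlap, from the text.**

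| Symptom type | Excluded Bristol mean | Eligible | Eligible and inside 3.5–4.5 |
|---|---|---|---|
| Constipation | above 4 | up to 4.0 | 3.5–4.0 |
| Diarrhea | below 4 | 4.0 and above | 4.0–4.5 |

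**2. Number per arm.** The protocol gives no power figure for this endpoint. Its calculation for the primary endpoint reproduces: n = 2(1.960 + 0.842)² × 0.412² / 0.244² = 44.76, so 45 per group, and 45/0.9 = 50 after dropout. I use 45 per arm.

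**3. Assumptions (none of these is in the protocol).** Let s be the share in range at baseline. Among out-of-range patients, 25% (control) and 55% (BBG9-1) are in range at follow-up. For in-range patients there are two scenarios:
- A: 80% stay in range in both arms, so treatment does nothing for them.
- B: 60% (control) and 85% (BBG9-1) stay in range, so treatment helps them too.

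**4. One case by formula (A, s = 20%).**
- Control: 0.2 × 0.80 + 0.8 × 0.25 = 0.36. BBG9-1: 0.2 × 0.80 + 0.8 × 0.55 = 0.60. The difference is 24 points instead of 30.
- Power = Φ[(d√n − 1.96√(2p̄(1−p̄))) / √(p₀(1−p₀) + p₁(1−p₁))], with d = 0.24, n = 45, p̄ = 0.48.
- = Φ[(1.610 − 1.385)/0.686] = Φ(0.328) = 0.63.

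**5. Power by simulation (200,000 trials per cell).** Order in each cell: unadjusted chi-square / CMH stratified by baseline in-range status / chi-square restricted to patients out of range at baseline.

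| s | Scenario A | CMH gain | Scenario B | CMH gain |
|---|---|---|---|---|
| 0% | 0.84 / 0.83 / 0.84 | none | 0.84 / 0.83 / 0.84 | none |
| 5% | 0.79 / 0.81 / 0.82 | 2 points | 0.82 / 0.83 / 0.82 | 1 point |
| 10% | 0.73 / 0.77 / 0.80 | 4 points | 0.81 / 0.83 / 0.80 | 2 points |
| 20% | 0.62 / 0.68 / 0.75 | 7 points | 0.79 / 0.82 / 0.75 | 4 points |
| 40% | 0.39 / 0.47 / 0.63 | 7–8 points | 0.76 / 0.81 / 0.63 | 6 points |

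**6. Sensitivity to the assumed rates.** I also tried 30% vs 60% and 25% vs 50% among out-of-range patients, with the same stay-in-range rate in both arms. If that rate is 60%, the CMH gain is only 2 to 3 points at s = 20% or 40%. If it is 90%, the gain is about 8 to 10 points at 20% and 8 to 11 at 40%. The more strongly baseline status predicts follow-up status, the more adjustment gains.

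**7. Validity.** With no treatment effect, the unadjusted test rejected in 4.5% to 5.5% of trials (s = 0%, 20% and 40%; out-of-range rates of 25% and 30%).

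**8. Where the loss comes from (A, s = 20%).** Power falls from 0.84 to 0.62, or 22 points. Stratifying recovers about 7. The other 15 or so come from including patients whom treatment is assumed not to affect, and no choice of test on all participants removes that part.

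**The case against.** The strongest case against is that nothing here is wrong in a strict sense. The protocol defines a status proportion, not conversion from abnormal to normal. Entry rests on symptoms, so some in-range patients follow from the chosen population, and staying in range is a legitimate outcome. Randomization balances baseline status in expectation. The endpoint is one of many exploratory ones, none of them powered, and details of method are left to a separate analysis plan.

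All of this stands, and it rules out several stronger readings that a reader might infer:

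- **That the comparison is biased or produces false positives.** It does not; see step 7.
- **That the treatment difference must shrink by the share already in range.** This holds only if treatment does nothing for in-range patients, which the protocol does not say. In scenario B at a 20% share the difference is 29 points (0.61 − 0.32), against 30 with nobody in range.
- **That the unadjusted test causes most of the lost power.** Under scenario A most of the loss is dilution.
- **That baseline Bristol score is thrown away.** Change and percent change in Bristol score from baseline form a separate secondary endpoint with its own Wilcoxon tests.
- **That the analysis should be restricted to patients out of range at baseline.** In scenario B at 20% this gives 0.75, below the 0.79 of the protocol's own test.

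The objection does not remove the narrower point. The protocol names an unadjusted test for this proportion, and stratifying by a value already in hand gained power in every scenario with some patients in range.

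**Conclusion.** The point holds as a minor improvement. The text shows that patients can enter already inside the normal range and that the named test takes no account of it. The between-arm comparison remains valid.

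The avoidable cost is about 4 to 7 points of power at an assumed 20% in-range share, 1 to 4 points at 5–10%, and roughly 6 to 8 points at 40%. These figures rest on 45 per arm, on 55% vs 25% among out-of-range patients, and on scenarios A and B. Other plausible rates move the 20% figure between about 2 and 10 points. If almost nobody enters in range, nothing is lost. The true share is not in the protocol, so the size cannot be fixed from it.

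The primary analysis of GSRS total score and the sample size are not affected.

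**What to change.** - **Main analysis.** Keep all participants. Replace the unadjusted chi-square or Fisher test for this endpoint with a CMH test stratified by baseline in-range status, or with logistic regression on treatment, baseline Bristol status and symptom type.
- **Reporting.** Give the share in range at baseline for each arm, and state that the endpoint is status at the follow-up examination.
- **Supplementary only.** Report normalisation among participants outside 3.5–4.5 at baseline. It answers a different question, uses fewer patients, and loses power if treatment also helps in-range patients stay in range.

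**Cost.** One or two sentences in the analysis plan, which the protocol says will be prepared before the data are fixed. No new data are needed, because the Bristol score is already used to determine eligibility. There is a small statistical price. A logistic model gives a conditional odds ratio instead of a difference in proportions, and strata may be sparse (at a 20% share, 0.2 × 45 = 9 in-range patients per arm). A CMH or standardised risk difference avoids most of this.
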